**Figure 1. f1:**
[figure not shown]
Plot describing the total sample size with power (1-β).

**Figure 2. f2:**
[figure not shown]
Plot showing central and non-central distributions.

### Eligibility criteria

Participants aged 18 and above years, both male and females, and those who self-reported non-specific neck pain for more than 3 months duration, and also present with weak power grip and/or impaired hand precision functions, and those who will be able to prospectively visit the study center will be invited to participate in the trial.

### Exclusion criteria

The exclusion criteria will be patients those who have history of receiving BFRT, deformity of upper extremity, spinal deformity, unhealed injuries in spine and upper extremity, uncontrolled hypertension, history of deep vein thrombosis and medically diagnosed neurological conditions that interfere with hand function or causes pain.

## Methods

Written informed consent will be obtained from all the participants who are eligible to be included in the study. The diagnosis of persistent neck pain will be made based on previous history and duration. Patients with radiating pain to shoulders or hands will be excluded. Enrolment, intervention, and assessment will be done as per the SPIRIT guideline (
Table 1). Participants will be obtained from the OPD of Physiotherapy Department and from all over the university including the teaching, non-teaching staff, from camps nearby and students. Ethical clearance has been obtained from Departmental Ethics Committee on 19/05/2023 with reference number DEC/PT/GU/2023 and the Trial has been registered with Clinical Trial Registry India CTRI/2023/06/053439. All patients diagnosed with chronic neck pain and weak hand function will sign the informed consent. Demographic data, history and other data will be obtained at the baseline. The study will be done in accordance to the declaration of Helsinki.
^
7
^

**Table 1. T1:** Schedule of enrolment, Intervention, and assessment, the SPIRIT guidelines.

Study period	Screening	Baseline (T0)	Training Sessions			Intervention Period in weeks								Post interventions Assessment (T1)	Follow up T2
Time (Weeks)	-4 to -1		S1 to S7	S8 to S16	S17 to S24	1	2	3	4	5	6	7	8	x	x
Patient Data	**x**														
Informed Consent	**x**														
Demographic Data	**x**														
Medical History	**x**														
Allocation		**x**													
Control group		**x**				**x**	**x**	**x**	**x**	**x**	**x**	**x**	**X**		**x**
Intervention group		**x**				**x**	**x**	**x**	**x**	**x**	**x**	**x**	**x**		**x**
Pressure pain Threshold		**x**												**x**	**x**
Hand Function		**x**												**x**	**x**
WHO5 INDEX		**x**												**x**	**x**
Compliance and motivation			**x**	**x**	**x**									**x**	
Patient Diary		**x**	**x**	**x**	**x**	**x**	**x**	**x**	**x**	**x**	**x**	**x**	**x**		
Routine PT	**X**	**x**													
Adverse Effects			**x**	**x**	**x**	**x**	**x**	**x**	**x**	**x**	**x**	**x**	**x**		

Note: The ‘x’ mark affirms the event, S – session, T0 – Baseline, T1 – Post-intervention recording, T2 – follow-up recording.

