### Intervention

All patients will receive standard physiotherapy care. It will include thermo therapy, neck isotonic exercises. The Experimental group will also receive BFR with single session with 75 vol LOP 40 to 50 % for upper grip ball exercise (Light resistance) wrist curls and wrist extension using long leavers Flexibar radial and ulnar deviation. Follow up will be done for the patients on second visit after 8 weeks and long-term follow up after 6 months for others on phones who fail to come for follow up. All the patients will be explained about the possible benefits and complete procedure of the study and consent will be signed by each patient who is willing to participate in the study. They will be told its voluntary and they can withdraw anytime from the study and it won’t affect their treatment if they refuse to be part of the study. Patient information will be kept confidential. Each individual will serve as self-control to report about the possible benefit in pain score after receiving BFRT and after follow up. See
Table 2 for the full BFRT protocol.
^
8
^

**Table 2. T2:** Protocol of BFR.

Mode of exercise prescription with BFR	
**Frequency**	2-3 times a week for 8 weeks
**Load**	20-40% 1RM
**Restriction time**	5-10 min per exercise (reperfusion between exercises)
**Type**	Small and large muscle groups (arms and legs/unilateral or bilateral)
**Sets**	2-4
**Cuff**	5 (small,) 10x 12 (medium), 17 or 18 (large)
**Repetitions Pressure**	(75 reps) – 30 x 15 x 15, or sets to failure 40-80 % AOP
**Rest between sets**	30-60 seconds
**Restriction form**	Continuous or intermittent
**Execution Speed**	1-2 (concentric or eccentric)
**Execution**	Until concentric failure or when planned rep scheme is completed

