## Discussion

The present study protocol presents a RCT testing the effectiveness of BFRT on pressure pain threshold and hand function among adults with persistent neck pain. The intervention aims to reduce pain and hand function by the proposed mechanism. The study intends to employ a randomized controlled trial design, ensuring scientific rigor and minimizing bias. By comparing the BFR training intervention group with a control group, researchers seek to assess the impact of this innovative technique on two primary outcomes: pressure pain threshold and hand function. Therefore, we expect that the adults with neck pain and compromised hand function in the BFRT group will exhibit improvement in terms of pain and hand function in comparison to the neck pain patients in the conventional group. The significance of this research lies in its potential to contribute valuable insights into managing neck pain and improving hand function using a novel approach like BFR training. If the results show positive effects, it could pave the way for a non-invasive, safe, and cost-effective intervention for individuals dealing with persistent neck pain. Ultimately, this study may have a meaningful impact on the quality of life for those suffering from this prevalent issue, offering hope for improved pain management and functional recovery.

**Study Status**: At the moment the authors are involved in training the assessors and physiotherapists those who will be involved in interventions and we are planning to start screening after one month.

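### Table 1 schedules adverse-effect recording only through week 8, so the follow-up that measures efficacy has no scheduled recording of harm

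*Protocol article*

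**What the plan says.** The protocol article sets its assessments out in Table 1 (Methods), a schedule with 15 time columns: screening, T0, three session blocks, weeks 1 to 8, T1 and T2. The table note gives the meaning of a mark: "The ‘x’ mark affirms the event, S – session, T0 – Baseline, T1 – Post-intervention recording, T2 – follow-up recording".

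The row "Adverse Effects" is marked in the session blocks and in every intervention week, and is empty at T1 and T2. The patient diary row also has its last mark at week 8. The row "Pressure pain Threshold" and the rows for hand function and WHO-5 are marked at T0, T1 and T2.

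The Intervention section describes the later contacts: "Follow up will be done for the patients on second visit after 8 weeks and long-term follow up after 6 months for others on phones", the phone being for those who do not attend. Table 2 gives the training period as "2-3 times a week for 8 weeks". The Exclusion criteria rule out people with "uncontrolled hypertension, history of deep vein thrombosis". The Discussion says that, should the results be positive, "it could pave the way for a non-invasive, safe, and cost-effective intervention for individuals dealing with persistent neck pain".

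**The concern.** The trial plans to see or phone both arms after treatment and to measure outcomes then, but its schedule provides no recording of adverse effects at those contacts. An event that begins after the last session, or one that begins during treatment and does not settle, has no scheduled place to be asked about or written down.

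At stake is the balance of the long-term picture. Objective III asks about the long-term effect of the training on grip. A report on that objective would have scheduled long-term outcome data and no matching adverse-effect data. Harms volunteered by participants might still reach the team, but unsolicited reports are not systematic. The article describes no sham cuff, so participants probably know their arm, and volunteered reports could differ between arms for that reason alone.

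**Working it through.** No figure in the plan needs reproducing here. The check is a reading of the schedule, with a small calculation of the length of the gap.

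**Step 1: is the blank real, or a product of broken table text?** The rows were aligned cell by cell with the 15 columns.

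| Row of Table 1 | Screening | T0 | Session blocks (3) | Weeks 1–8 | T1 | T2 |
|---|---|---|---|---|---|---|
| Adverse effects | – | – | x | x | – | – |
| Patient diary | – | x | x | x | – | – |
| Compliance and motivation | – | – | x | – | x | – |
| Pressure pain threshold | – | x | – | – | x | x |
| Hand function | – | x | – | – | x | x |
| WHO-5 | – | x | – | – | x | x |

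The adverse-effects row has 15 cells for 15 columns, with 3 + 8 = 11 marks and four blanks (screening, T0, T1, T2). The pressure pain threshold row aligns in the same way and puts its marks where one would expect them. The blanks at T1 and T2 are therefore what the schedule states.

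**Step 2: are items collected by session simply not carried to T1 by convention?** No. Compliance and motivation is also collected in the session blocks, and it is marked at T1.

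**Step 3: does another part of the article schedule later collection?** No. The Intervention section describes the follow-up contacts without mentioning adverse effects, and frames what participants report there as possible benefit in the pain score. Objectives, Outcome measures and Statistical analysis do not mention adverse effects.

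**Step 4: how long is the gap?** Table 1 gives neither T1 nor T2 a week number. Assume that T1 directly follows week 8, that T2 is the six-month contact, and that six months is about 26 weeks.

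- Six months counted from baseline: 26 − 8 = 18 weeks without scheduled recording.
- Six months counted from the end of treatment: 8 + 26 = 34 weeks in total, and 34 − 8 = 26 weeks without scheduled recording.

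Under the same assumption the T1 blank costs little, because week 8 itself is marked. The gap that matters is from T1 to T2.

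**The case against.** The strongest reply is that recording adverse effects during exposure is a legitimate choice. All 8 treatment weeks are covered, nothing in the article contradicts that choice, and neither the primary comparison nor any stated objective depends on later adverse-effect data. That stands, and it makes this an inexpensive improvement, with no effect on the validity of the main result.

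It can also be said that the trial does not follow benefit alone after treatment. Pressure pain threshold, hand function and WHO-5 can worsen as well as improve, so greater pain sensitivity, lost function or lower well-being would show in both arms. That stands too. It does not cover events of another kind, such as the vascular problems that the exclusion criteria have in view.

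Several stronger readings are tempting, and the article does not support them:

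- **That a safety claim is planned.** The word appears once, in a conditional outlook in the Discussion. No objective, hypothesis, primary outcome or analysis concerns safety.
- **That later harms will never be collected.** The table shows what is scheduled. It does not bar recording a volunteered report, and the handling of such reports may be left to a full protocol that is not shown.
- **That the adverse-effect rate will be understated.** No rate or window is defined, and a treatment-period rate is not understated for its own period.
- **That the Introduction names deterioration as a risk of this training.** It attributes increased pain and possible deterioration to resistance training at increased loads, and presents blood flow restriction as the low-load alternative.
- **That the uncovered share of calendar time measures missed harm.** It does not. The article gives no information on when harms would appear, and excluding people with a history of thrombosis does not establish a delayed effect.

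**Conclusion.** The point holds in a limited form. Adverse effects and the diary are scheduled through week 8 only, while T1 and T2 measure pressure pain threshold, hand function and WHO-5. Harms that arise or persist after treatment are thus not systematically collected in either arm, and the Discussion's conditional wording on safety would have no scheduled post-treatment adverse-effect data behind it.

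The gap is close to nil at T1 and about 18 to 26 weeks at T2. Those lengths rest on the assumptions that T1 directly follows week 8 and that T2 is the six-month contact, and on whether the six months run from baseline or from the end of treatment. The finding itself rests only on the blank cells. How many events fall in the gap cannot be estimated from the article.

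**What to change.** In Table 1, mark the adverse-effects row at T1 and T2 for both arms. Put the same adverse-effect question, in the same words, to participants reached by phone at six months. State in the report the window over which adverse effects were observed, so that any remark on safety can be read against it.

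The cost is one line in the schedule and a few minutes at contacts that are already planned. No visit is added and no treatment changes. The Discussion's study-status note says that screening had not begun, so the change could be made before the first participant; information not asked for at follow-up is hard to recover reliably afterwards.

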### Intervention

All patients will receive standard physiotherapy care. It will include thermo therapy, neck isotonic exercises. The Experimental group will also receive BFR with single session with 75 vol LOP 40 to 50 % for upper grip ball exercise (Light resistance) wrist curls and wrist extension using long leavers Flexibar radial and ulnar deviation. Follow up will be done for the patients on second visit after 8 weeks and long-term follow up after 6 months for others on phones who fail to come for follow up. All the patients will be explained about the possible benefits and complete procedure of the study and consent will be signed by each patient who is willing to participate in the study. They will be told its voluntary and they can withdraw anytime from the study and it won’t affect their treatment if they refuse to be part of the study. Patient information will be kept confidential. Each individual will serve as self-control to report about the possible benefit in pain score after receiving BFRT and after follow up. See
Table 2 for the full BFRT protocol.
^
8
^

**Table 2. T2:** Protocol of BFR.

Mode of exercise prescription with BFR	
**Frequency**	2-3 times a week for 8 weeks
**Load**	20-40% 1RM
**Restriction time**	5-10 min per exercise (reperfusion between exercises)
**Type**	Small and large muscle groups (arms and legs/unilateral or bilateral)
**Sets**	2-4
**Cuff**	5 (small,) 10x 12 (medium), 17 or 18 (large)
**Repetitions Pressure**	(75 reps) – 30 x 15 x 15, or sets to failure 40-80 % AOP
**Rest between sets**	30-60 seconds
**Restriction form**	Continuous or intermittent
**Execution Speed**	1-2 (concentric or eccentric)
**Execution**	Until concentric failure or when planned rep scheme is completed

### Outcome measures

**
*Pressure pain threshold using Algometer*
**

Using an algometer, a portable instrument that measures pressure sensitivity at particular anatomical locations in the neck region, the pressure pain threshold (PPT) will be determined. The algometer consists of a gauge with a pressure-sensing tip attached that measures applied pressure in kilopascals (kPa). Before the assessments begins, the algometer will be calibrated to ensure accuracy and consistency of measurements. Participants will be comfortably seated in an upright position with their neck muscles relaxed. It is essential to explain the procedure to the participant, ensuring they understand the assessment and can provide feedback on their pain perception. Specific anatomical points in the neck region will be chosen for the assessment. Commonly, these points include the trapezius, levator scapulae, and sternocleidomastoid muscles. The researcher will progressively apply pressure to the selected spots using the algometer. A button must be pressed to cease the pressure application or the participant must verbally report feeling pain for the pressure to increase at a constant rate (for example, 1 kPa/s).

**
*Neck Outcome Score*
**

The Neck Outcome Score (NOS) is a self-reported questionnaire that assesses various aspects of neck pain and its impact on daily activities and quality of life. Participants will be provided with the NOS questionnaire, and the research team will explain its purpose and how to complete it. It’s important to ensure that participants understand the questions and how to score their responses accurately. The NOS typically includes questions related to pain intensity, pain-related disability, functional limitations, and the impact of neck pain on quality of life.

**
*Grip strength using hand help dynamometer*
**

Grip strength will be measured using a handheld dynamometer. We will ensure that the participant is well-rested and not fatigued before the measurement. We will also inform the participant about the purpose of the grip strength measurement and the procedure involved. The dynamometer will be adjusted to fit the participant’s hand size. The participant will be seated on a chair without armrests, ensuring proper posture with their back straight, feet flat on the ground, and forearm resting on a flat surface. We will instruct the participant to hold the dynamometer in their dominant hand. When the participant is ready, they should be instructed to squeeze the dynamometer handle with maximum effort for about 3 to 5 seconds. The researcher can provide encouragement to the participant during the measurement to ensure they exert their maximum effort. The highest grip strength measurement achieved during the trial will be recorded.

**
*WHO-5 quality of life index questionnaire*
**

The WHO-5 quality of life index questionnaire is used to assess an individual’s subjective well-being and quality of life. We will briefly explain the purpose of the WHO-5 questionnaire to the participant and let them know that it’s designed to assess their emotional well-being and quality of life. Participants will rate their agreement with each statement on a scale from 0 to 5, where 0 indicates “at no time” and 5 indicates “all of the time”. After participants have provided their responses, we can assist them in calculating their total score. A higher score on the WHO-5 indicates better emotional well-being and quality of life.

### Statistical analysis

Data will be analysed using IBM Statistical Package for Social Sciences version 21 for Windows. The patient characteristics at the baseline will be presented as mean, standard deviation and proportion with 95% confidence interval. The kolmogorov-smirnov and Shapiro Wilk test will be performed to assess the normality distribution of all the outcome scores. The student’s t- test and paired t-test will be used to compare between the groups and intra group and multiple regression analysis will be done to check for any correlation or any factor influencing the outcomes of the study.

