### Null hypothesis

There is no difference between the BFRT and conventional physiotherapy group in alleviation of pain, and hand function among adults with neck pain.

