### Alternate hypothesis

BFRT will have a significant impact in reducing pressure pain threshold and improving hand function in patients with persistent neck pain among adults.

**
*Subjects*
**

One hundred and ten self-reporting persistent neck pain for more than three months duration will be screened for eligibility and recruited in the study. After obtaining informed consent, the participants will be randomly allocated in 1:1 ratio to the BFR training group and the control group using a computer-generated randomization sequence. Allocation concealment will be ensured to maintain blinding and reduce potential bias. Sample size was calculated using Gpower version 3.1.9.4 for Windows by assuming effect size of 0.5(Cohen’s D medium size effect was assumed) with the margin of error (α) to test the level of significance was set at 0.05 and (1-α) 80% βpower and confidence interval at 95%, the final derived sample with added 10% of contingency was n=112
^
6
^ (
Figure 1). See
Figure 2 for central and non-central distributions.

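### Make the main between-arm comparison baseline-adjusted, and do not read benefit from within-arm before/after tests

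*Protocol article*

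**What the plan says.** The Statistical analysis section states that Student's "t- test and paired t-test will be used to compare between the groups and intra group". It does not say whether the between-group test is run on post-intervention values or on changes. Regression appears only with an exploratory purpose: "multiple regression analysis will be done to check for any correlation or any factor influencing the outcomes of the study". Neither treatment arm nor the T0 value is named as a term in it.

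Table 1 (Methods) marks PPT, hand function and WHO-5 at three times: "T0 – Baseline, T1 – Post-intervention recording, T2 – follow-up recording". Baseline values of these outcomes will therefore be available.

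The Intervention section adds: "Each individual will serve as self-control to report about the possible benefit in pain score after receiving BFRT and after follow up". The same section says "All patients will receive standard physiotherapy care", with BFRT added in the experimental group.

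The Null hypothesis is between-group: "There is no difference between the BFRT and conventional physiotherapy group in alleviation of pain, and hand function among adults with neck pain". The Discussion likewise expects improvement in the BFRT group relative to the conventional group.

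**The concern.** There are two separate issues.

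**Efficiency.** When an outcome is measured before randomised treatment and is correlated with its later value, a t-test that does not adjust for it leaves explainable variance in the error term. The estimate is unbiased and the type I error is correct, but the confidence interval is wider than necessary.

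**Interpretation.** A before/after change within the BFRT arm contains the effect of BFRT, the effect of the standard physiotherapy that both arms receive, and the natural course of neck pain. A paired p-value cannot separate these. Using patients as self-controls to report benefit answers a different question from the stated null hypothesis. It could put a claim of benefit into the report that the randomised comparison does not support.

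**Working it through.** **Inputs from the protocol**
- Effect size: "effect size of 0.5(Cohen’s D medium size effect was assumed"; α = 0.05, power 80%, 10% contingency, n = 112 (under Alternate hypothesis).
- 110 patients to be randomised 1:1 (Abstract), so 55 per arm.

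**Assumptions, because the protocol gives no figure**
- T0–T1 correlation r = 0.3, 0.5 or 0.7.
- Two-sided testing at 0.05; sidedness is not stated.
- Equal SDs at T0 and T1.

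**The plan's own figure.** A two-sample t-test with d = 0.5 and 80% power needs 51 per arm at one-sided 0.05. Then 102 × 1.10 = 112.2, which gives 112. At two-sided 0.05 it needs 64 per arm, and 128 × 1.10 = 140.8. The stated 112 therefore matches a one-sided calculation on unadjusted values.

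**Between-arm power at 55 per arm.** Power comes from the noncentral t distribution with 108 df (two-sided critical value 1.982). The noncentrality is d* × √(55/2) = d* × 5.244, where
- post values: d* = 0.5
- change scores: d* = 0.5/√(2(1−r))
- ANCOVA: d* = 0.5/√(1−r²) (the one further df used by the covariate is neglected)

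| r | Post values: d*, noncentrality, power | Change scores | ANCOVA |
|---|---|---|---|
| 0.3 | 0.500, 2.62, 74% | 0.423, 2.22, 59% | 0.524, 2.75, 78% |
| 0.5 | 0.500, 2.62, 74% | 0.500, 2.62, 74% | 0.577, 3.03, 85% |
| 0.7 | 0.500, 2.62, 74% | 0.645, 3.39, 92% | 0.700, 3.67, 95% |

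ANCOVA has the highest power in every row, so the efficiency point holds whichever version of the t-test is meant. At r = 0.3 the gain over post values is only about 4 points, and at r = 0.7 the gain over change scores is only about 3 points. At one-sided 0.05 the unadjusted post-value power is 83%.

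**Within-arm paired test, no BFRT effect.** Suppose both arms improve by the same g SD. In the BFRT arm (n = 55, 54 df, critical value 2.005) the noncentrality is g/√(2(1−r)) × √55. At r = 0.5 the SD of change is √(2 × 0.5) = 1, so
- g = 0.2: 0.2 × 7.416 = 1.48, significant improvement in 31% of trials
- g = 0.3: 0.3 × 7.416 = 2.22, significant improvement in 59% of trials

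Over r = 0.3 to 0.7 the range is 23–47% for g = 0.2 and 45–81% for g = 0.3. The size of any common improvement is not in the protocol; 0.2–0.3 SD is illustrative.

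**The case against.** The strongest defence is that the randomised comparison is sound. The hypothesis is between-group, a between-group test is named, and an unadjusted t-test in a randomised trial controls type I error. Covariates are commonly settled in a statistical analysis plan, which is not shown. All of this stands, and it limits the first issue to an improvement. It does not remove the second, because the self-control sentence states a purpose for the within-person comparison.

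A reader might also infer four stronger things that the protocol does not support.
- *Baseline is ignored.* The paired test uses T0, the between-group t-test could be run on changes, and the planned regression could include T0. What is missing is a baseline-adjusted test named for the treatment effect.
- *The trial falls short of its stated power, so adjustment is needed to rescue it.* The 74% depends on two-sided testing. The protocol does not state sidedness, and at one-sided 0.05 the power is 83%.
- *Regression to the mean will by itself make the paired tests significant.* Patients must "also present with weak power grip and/or impaired hand precision functions", but no cut-off is given and either impairment suffices. Screening (weeks −4 to −1) is separate from T0, so any such shift may occur before T0. No PPT threshold governs entry. The effect is possible for hand function, but it cannot be sized from the document.
- *Benefit will be declared if the BFRT arm is significant and the control arm is not.* No such rule is stated.

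**Conclusion.** The point holds as a should-fix, not as a fatal flaw. The between-arm t-test is valid but inefficient: under the assumptions above, ANCOVA adds about 4, 11 or 21 percentage points of power over post values at r = 0.3, 0.5 or 0.7, and it is also better than change scores at each r. The size of the gain rests wholly on r, which the protocol does not give.

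The self-control sentence conflicts with the between-group hypothesis. A significant paired result in the BFRT arm is not evidence for BFRT when everyone receives standard physiotherapy. This conclusion needs no numerical assumption; the 31–59% only illustrates how often such a result could arise with no BFRT effect.

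**What to change.** - Make the main analysis of each outcome a between-arm ANCOVA of the T1 value on arm and T0 value, or a mixed model over T1 and T2 with T0 as covariate. Report the adjusted difference with its 95% CI.
- Delete the self-control sentence from the Intervention section, or reword it so that benefit is judged by the difference between arms.
- Report within-arm changes descriptively, without claims of benefit.

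The cost is wording only. The T0 values are already scheduled, so no new data or visits are needed, and the software named in the protocol can fit these models. The Study Status note says that screening had not begun, so at that point the change could be made before any outcome data existed.

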**Methods:**

This study will be a prospective 1:1 allocation, parallel group active controlled trail conducted at Physiotherapy Department, Galgotias University. The trial was prospectively registered with the Clinical Trial Registry India CTRI/2023/06/053439. Informed consent will be obtained from all the participants who are eligible to be included in the study. A total of 110 patients with persistent neck pain will be randomly allocated into two groups. The BFRT group will receive supervised training sessions three times a week for eight weeks, performing low-load resistance exercises with blood flow restriction applied using personalized cuff pressure. The control group will receive standard care for neck pain, which may include general advice, manual therapy, and/or home exercises without BFRT. The primary outcome measures will be the pressure pain threshold, assessed using a pressure Algometer, and hand function, evaluated using standardized tests such as Hand Grip Strength and Purdue Peg board Test.

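### T-tests are the only comparison fixed for three-visit data with expected non-attendance; the T2 comparison of in-person outcomes may rest on attenders and is biased if absence follows outcome differently by arm

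*Protocol article*

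**What the plan says.** The note to Table 1 of the protocol article defines three recordings: "T0 – Baseline, T1 – Post-intervention recording, T2 – follow-up recording". The table schedules pressure pain threshold (PPT), hand function and the WHO-5 at all three.

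For comparisons, the Statistical analysis section states that Student's "t- test and paired t-test will be used to compare between the groups and intra group". The only other model named has a different purpose: "multiple regression analysis will be done to check for any correlation or any factor influencing the outcomes of the study".

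The Intervention section foresees non-attendance and provides "long-term follow up after 6 months for others on phones who fail to come for follow up". It gives no expected rate.

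The abstract says: "The primary outcome measures will be the pressure pain threshold, assessed using a pressure Algometer, and hand function", the latter by grip strength and the Purdue pegboard. All of these need the patient to be present. Objective III concerns the long-term effect on precision and power grip, so it depends on such measures at the late visit.

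**The concern.** A two-sample t-test takes one number per patient. Applied to T2 values, it uses neither the patient's T0 value nor the T1 result of someone who does not return, although both have been collected. For PPT, grip and pegboard a phone call leaves the T2 value empty. Unless a missing-data rule exists elsewhere, the T2 comparison is then between those who came back, not between the groups as randomised.

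Two things are at stake. If return depends on how the patient did by T1, and does so differently in the two arms, the T2 difference is biased and the nominal 5% error rate is not kept. If return is unrelated to outcome, or related in the same way in both arms, there is no bias, but the test has less power than the recorded data allow.

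**Working it through.** **The plan's own figure.** The sample size section assumes d = 0.5 with α "set at 0.05 and (1-α) 80% βpower". A one-sided two-sample t-test needs 51 per arm, 102 in total; 102 × 1.1 = 112.2, which reproduces the stated 112. A two-sided test needs 128, and 128 × 1.1 = 140.8, which does not. So the plan was sized for a t-test at one time point. Its only allowance for loss is the 10% contingency.

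**Inputs from the document.** Three visits; 110 randomised 1:1, so 55 per arm; d = 0.5; 10% contingency.

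**Inputs assumed (none is in the document).** Outcome SD 1; correlations T0–T1 0.6, T0–T2 0.5, T1–T2 0.7; T2 absence of 10%, 20% or 30%; T1 complete; where absence is linked to outcome, each 1 SD worse T1 result raises the log-odds of absence by 1.

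**Bias with no true effect.** If T1 governs absence in one arm, the attenders' mean T2 in that arm shifts by

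bias = corr(T1,T2) × E[T1 | present].

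E[T1 | present] from the logistic model is 0.091, 0.173 and 0.253 SD at 10%, 20% and 30% absence. Multiplying by 0.7 gives 0.06, 0.12 and 0.18 SD. Simulation of the two-sided T2 t-test (4,000 trials per scenario) agrees within Monte Carlo error; rejection rates move by up to about one percentage point between runs.

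| Link between T1 result and absence | Absent | Bias (SD) | Type I error |
|---|---|---|---|
| BFRT arm only | 10% | about 0.07 | about 7% |
| BFRT arm only | 20% | about 0.12 | about 9% |
| BFRT arm only | 30% | about 0.18 | about 13% |
| Opposite in the two arms (extreme) | 20% | about 0.24 | about 21% |
| Opposite in the two arms (extreme) | 30% | about 0.36 | about 36% |
| Same in both arms, or random | 10–30% | 0 | about 5% |

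A steeper link (log-odds 1.5 per SD) in one arm only gives 0.09, 0.16 and 0.23 SD, and 6.9%, 11.6% and 16.5%. A weaker contrast (1 in BFRT, 0.5 in controls) at 20% absence gives 0.055 SD and 5.4%.

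At the 20–30% absence rates, adjusting the attenders-only test for T0 leaves 0.07 to 0.22 SD of bias across the one-arm and opposite-link scenarios. An estimate using T0 and T1 from all randomised patients is biased by less than 0.005 SD and rejects in about 5%.

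**Power with 20% random loss, d = 0.5, two-sided 5%.** 55 × 0.8 = 44 attend per arm.

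- T-test: noncentrality 0.5 × √(44/2) = 2.35; power 64%.
- Attenders adjusted for T0: residual variance 1 − 0.5² = 0.75, so d becomes 0.5/√0.75 = 0.577; noncentrality 0.577 × √22 = 2.71; power 76% (75–77% by simulation).
- All visits: given T0, the T1–T2 correlation is (0.7 − 0.6 × 0.5)/(√0.64 × √0.75) = 0.577, squared 0.333. The variance factor is 0.667/0.8 + 0.333 = 1.167, against 1/0.8 = 1.25 for attenders only. Noncentrality 0.577 × √(27.5/1.167) = 2.80; power 79%.

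Of the 15 points gained, about 12 come from the T0 covariate and about 3 from using T1.

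**The case against.** The protocol does not say that the tests are run visit by visit on attenders only, defines no analysis set and gives no rate of loss. Such rules are commonly left to an analysis plan or full protocol that is not shown, and a t-test can be run on imputed data. This stands: attenders-only analysis is an inference, and the absence of a missing-data rule is not itself a fault. What remains is the method that the article does fix.

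A reader might infer that the T2 result will show an effect that does not exist. The documents do not support that. A false effect needs the link between outcome and absence to differ by arm. Only one arm receives the added cuff training, which makes this plausible, but nothing in the text shows it. With equal links there is no bias, and at 10% absence, the plan's own contingency, the one-arm link costs only about 0.07 SD.

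A reader might also extend the point to every outcome and visit. The WHO-5 and Neck Outcome Score are questionnaires that could be completed by phone, and the non-attendance text concerns follow-up, not T1. The bias argument is therefore limited to PPT, grip and pegboard at T2.

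The t-test might also be meant for change from baseline, which would use T0. With the assumed T0–T2 correlation of 0.5, the variance of the change is 2 − 2 × 0.5 = 1, the same as for the raw value, so nothing is gained, and absent patients still drop out.

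Finally, most of the power gain needs only a T0 covariate. That is correct, but the covariate alone does not remove the bias that arises when absence depends on T1.

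**Conclusion.** The point holds in a conditional form. T-tests are the only comparison fixed for T0/T1/T2 data, non-attendance at follow-up is foreseen, and phone contact cannot supply the in-person primary outcomes. Unless missing values are handled elsewhere, the T2 comparison of PPT and hand function rests on attenders.

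If absence follows the T1 result in one arm only, the bias of 0.07 to 0.18 SD is 14% to 36% of the planned 0.5 SD (0.07/0.5 and 0.18/0.5), with type I error of about 7% to 13%. Opposite links are an extreme case, not an expectation. With random absence, or the same link in both arms, the cost is power only: about 64% against 79% at 20% random loss. The sizes rest on the assumed correlations, absence rates and link strength; the direction of the comparison between methods did not change in any scenario tried. This is an improvement the plan should make, not a fatal flaw.

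**What to change.** Make the between-arm comparison of each repeatedly measured outcome a linear mixed model for repeated measures. Use all T1 and T2 values of every randomised patient in the assigned arm, with the T0 value, visit, arm and arm-by-visit as terms and an unstructured covariance. Read the T1 and T2 arm differences from this model, and keep the t-tests as sensitivity analyses at most.

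The cost is one paragraph of analysis text and slightly more analysis work; no new data and no change to the stated sample size are needed. The Study Status paragraph says that screening had not begun, so the change could be made before any data were seen. The limitation should be written down with it: the model assumes that absence is explained by the recorded T0 and T1 values, and it does not remove bias if absence depends on the unseen T2 value.
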